### Concealment mechanism {16b}

Allocation concealment will be achieved using sequentially numbered, opaque sealed envelopes [17]. Participants will be assigned in two intervention groups: a football group and aerobic group in a 1:1 ratio. Allocation concealment will be ensured. The randomization code will not release until the participants have been recruited into the trial, which takes place after all baseline measurements have been completed.

### Implementation {16c}

The responsible committee for recruitment will send a form to the independent researcher who is not involved in any assessment of the outcome of the study. This form will include a randomization number with closed envelopes. The responsible staff for recruitment is not allowed to receive information about group allocation.

All participants who give consent for participation and who fulfill the inclusion criteria will be randomized. Randomization will be requested by an employer who is responsible for this process from Tishreen University by using randomization software [17]. Each participant of the trial will be given a unique numeric code with the three code length character by the independent researcher.

## Assignment of interventions: blinding

### Who will be blinded {17a}

Due to the nature of the intervention, neither participants nor staff can be blinded to allocation, but are strongly encouraged not to disclose the allocation status of the participant at the follow-up assessments.

### Procedure for unblinding if needed {17b}

The design is open label with only outcome assessors being blinded, so unbinding will not occur.

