### Strategies to improve adherence to interventions {11c}

The adherence reminder sessions will take place 15 min before every training session. This session will include the following:
The importance of following a training program for general health.Instructions about how to practice carefully and how to avoid physical collision between participants, especially in competitions or games.The importance of adherence in order to develop the performance of the body, and the negative effects of absence from any training session.Instructions about the purpose of the study and the training plan.Instructions the importance of informing the coach about any injury or physical pain.Participants will have an opportunity to ask questions throughout the training program at any time.

Before the starting of every single month of the training program, there will be a special recreational trip in order to increase the motivation and commitment of participants.

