#### PA

The PA of the rectus femoris, vastuss lateralis, and vastus medialis will be measured using B-mode ultrasound at the same site as MT and CSA [1]. The transducer will be longitudinal to the muscle tissue interface, and 1 image will be analyzed offline. Muscle fiber will be determined as the intersection of the fascicles with the deep aponeurosis.

PT length will be measured via ultrasound scans (Esaote, Technos MPX, ultrasound) at knee joint angle of 90° (0° corresponding to full extension), as the distance between tendon insertions on the patella apex and the tibial tuberosity. Tendon CSA will be measured from transversal ultrasound scans (linear array transducer 5 cm, LA523, 10 MHz transducer). The reliability of this technique has been shown previously [45]. PT CSA is obtained as the average of two measurements performed at the proximal (CSAp) and distal (CSAd) insertions and at tendon mid-length (CSAm). The mean CSA of these three scans’ positions will be used for further analysis. PT length will be measured as the distance between the proximal insertion of the PT and the tibial insertion. The use of ultrasound to perform quantitative measurements of musculoskeletal tissues has shown reliability (tendon CSA: ICC of 0.91–0.98 and 0.96–0.98 for tendon length) [20].

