#### Yo-Yo intermittent recovery test

Once the configuration of the tests has been set up, test principal investigator/officials are positioned at both shuttle lines (cone B and C), and participants are ready, then the test will begin. Participants begin the test from cone B. When instructed by the audio player, they must run towards cone C (this must be reached before the following beep signal) and immediately return to cone B before the next signal. Once cone B is reached, participants then have a 10-s recovery period in which they must jog from cone B towards cone A, and then back to cone B before the commencement of the next shuttle. In this test, the participants are only allowed two consecutive failed attempts before they are withdrawn from the test. That being, if the individual fails to reach cone C and back to cone B in the allocated time, one fail is issued. If this happens a second consecutive time, then they are eliminated. Once withdrawn from the test, the individual’s score must be recorded. The YYIR1 typically lasts for 5–15 min [28]. The test is comprised of 91 shuttles and can last up to approximately 29 min; however, it is very unlikely somebody will complete it. Scores can be presented in three ways: (1) total distance (meters), (2) level achieved, or (3) VO2 max. Total distance is more simple to understand and calculate, whereas level achieved is more complex as the test begins at level 5 and then skips to level 9 at the beginning.

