### Methods for additional analyses (e.g., subgroup analyses) {20b}

The statistical analysis is performed by an independent statistician, blinded for the group allocation by the end of the retest procedure. Perhaps there will be none, the group is not large but perhaps you are looking at differences based on area men live, if they previously played team football, etc.

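### The protocol's statements on who is blinded do not agree, and no masking to arm or visit is stated for the offline reading of the primary ultrasound images

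*Protocol article*

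**What the plan says.** Three sections of the protocol article bear on who is blinded.

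- Who will be blinded {17a}: "neither participants nor staff can be blinded to allocation, but are strongly encouraged not to disclose the allocation status". The request applies to the post-training visit. No blinded role is named.
- Procedure for unblinding if needed {17b}: "The design is open label with only outcome assessors being blinded, so unbinding will not occur".
- Methods for additional analyses {20b}: "The statistical analysis is performed by an independent statistician, blinded for the group allocation by the end of the retest procedure".

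Other safeguards are stated. Under Implementation {16c}, allocation is handled by an "independent researcher who is not involved in any assessment of the outcome of the study", who also gives each participant a numeric code. Under Concealment mechanism {16b}, the code is released only after all baseline measurements. Under Confidentiality {27}, participant files carry individual codes.

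Outcomes {12} lists muscle cross-sectional area, fascicle length, muscle thickness and pennation angle under the primary outcome. According to Plans for assessment and collection of outcomes {18a}, fascicle length requires the reader to identify a clear fascicle, cross-sectional area is traced with a polygon tool in ImageJ, and for pennation angle "The transducer will be longitudinal to the muscle tissue interface, and 1 image will be analyzed offline". The same examiner performs the measurements at both visits. Nothing is said about whether the image reader can see the man's identity, arm or visit.

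Statistical methods {20a} plans a paired t test within each group and an independent-samples t test between groups before and after the intervention. No baseline adjustment is mentioned.

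**The concern.** Taken literally, {17a} leaves nobody blinded, {17b} leaves only the assessors blinded, and {20b} adds someone whom the word *only* in {17b} excludes. These sections exist to settle the question, so a condensed article does not explain the disagreement. As it stands, one cannot tell whether the person who picks the fascicle, traces the area or measures the angle is covered by the blind.

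This matters because these readings involve choice and are primary outcomes. At follow-up, after 12 weeks of openly different training, the stated protection depends on the discretion of people who know the allocation. Images read offline can be protected by procedure instead, and the article does not say that they are.

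Two routes for bias follow. A reader who knows which image is the post-training one may tend to see a change. A reader who knows the arm may tend to see a difference between arms.

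**Working it through.** **1. Who is blinded**

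| Role | {17a} | {17b} | {20b} |
|---|---|---|---|
| Participants | no | no (open label) | – |
| Staff | no | only outcome assessors are | – |
| Statistician | not mentioned | excluded by *only* | yes |

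The entries for staff can be reconciled if staff means those who deliver the training. The entry for the statistician conflicts with {17b} as worded.

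**2. What protects the assessor at follow-up**

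The independent researcher and the late release of the code protect concealment and keep allocation knowledge away from the acquisition of baseline scans. They do not by themselves keep an assessor unaware of the arm 12 weeks later. The file codes are not said to be applied to images or to hide arm or visit. The non-disclosure request is what remains.

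**3. How each kind of knowledge reaches the planned tests**

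- *Visit known, arm unknown.* Let every post-training reading be shifted by v in both arms. Each paired test then estimates (true change + v). The between-arm difference at follow-up contains v − v = 0. The harm is to the within-arm tests, and the between-arm contrast is largely spared.
- *Arm known at follow-up.* Let readings in one arm be shifted by b. The independent t test after the intervention then estimates (true difference + b), so b enters in full.

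**4. Illustration of the second route**

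Inputs from Sample size {14}: pilot means for vastus medialis pennation angle 10.59 and 8.17, SDs 2.80 and 2.01, planned 30 per arm, 15% dropout (60 × 0.85 = 51, so about 25 per arm).

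- Pooled SD: s = √[(2.80² + 2.01²)/2] = 2.437.
- Check against the plan: (10.59 − 8.17)/2.437 = 2.42/2.437 = 0.993. The protocol states 0.992, so the scale agrees.

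Assume no true difference and a two-sided 5% t test, with df = 2n − 2 and noncentrality δ = (b/s)·√(n/2). The rejection probability is P(|T′| > t₀.₉₇₅), where T′ is noncentral t. The critical value is 2.002 for n = 30 (df 58) and 2.011 for n = 25 (df 48).

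For b = 0.5° and n = 30: b/s = 0.205 and δ = 0.205 × √15 = 0.79. The rejection probability is 12.2%.

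| Assumed shift b | b/s | b as share of 2.42° | False positives, 30 per arm | 25 per arm |
|---|---|---|---|---|
| 0 | 0 | 0% | 5.0% | 5.0% |
| 0.25° | 0.10 | 10% | 6.8% | 6.5% |
| 0.5° | 0.21 | 21% | 12.2% | 11.0% |
| 1.0° | 0.41 | 41% | 34.6% | 29.6% |

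The shifts are assumptions. The document gives no figure for reading bias.

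**The case against.** The strongest reply is that the blind is declared and that the gap is one of detail. {17a} ties the lack of blinding to the nature of the intervention, and asking people not to disclose at follow-up makes sense only if the assessors are other, blinded people, as {17b} says. Allocation is kept apart from assessment, files are coded and the statistician is independent. A journal article often leaves image handling to the full protocol. Much of this stands. The conflict between {17a} and {17b} may be one of wording, and silence on masking does not show its absence.

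Several stronger readings are therefore not supported:

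- *The images are unmasked.* The article does not say so. It says nothing either way.
- *The blind rests on the men's silence alone.* The request covers staff too, and allocation is handled by someone with no assessment role.
- *The reader must know the visit because one examiner takes both scans.* No section says that the examiner who scans is the person who later reads the images in ImageJ. Using one examiner also serves reliability.
- *Knowing the visit distorts the football-versus-aerobic comparison.* A shift common to both arms largely cancels there.
- *Reminders before each session make men try harder in the favoured arm.* The reminder list includes "Instructions about the purpose of the study and the training plan", but it is described without any difference between arms, and nothing says that men are told to expect more from football. Effort cannot change an ultrasound measure taken at rest.
- *Unblinded investigators judge the Yo-Yo test.* The text has "test principal investigator/officials are positioned at both shuttle lines (cone B and C"), in a generic description of a secondary, audio-paced test. Whether these people are blinded is not stated.

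The reply does not meet two points. The statements on who is blinded still disagree as written, and the declared blind has no stated procedure at follow-up beyond a request, although the readings are offline and could be masked directly.

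**Conclusion.** The point holds in a limited form. The three statements on blinding need reconciling, and the protocol does not show that its claim of blinded assessment extends to the reading of the primary ultrasound images. This is an open route for reader bias, not evidence that bias will occur.

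Its size cannot be derived from the document. Over assumed arm-related shifts of 0.25° to 1.0° in pennation angle, the false-positive rate with 30 per arm runs from about 7% to about 35%, with about 12% at 0.5°. These figures assume no true difference, the pilot SDs, a two-sided 5% test and a systematic shift by a reader who knows the arm, which means that the declared blind has failed. If arm is hidden and only the visit is known, the exposure is mainly in the within-arm paired tests. If masked reading is already part of the full protocol, one sentence settles that part. The change is worth making because it is cheap.

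**What to change.** 1. Store every scan under a random image code, with any on-screen name or date removed. After the last post-test, read all pre and post images in one batch, in random order, with identity, arm and visit hidden. Let the independent researcher named under Implementation {16c} hold the key until the readings are final.
2. Align {17a}, {17b} and {20b}. State which roles are blinded (who scans, who reads the images, who runs the dynamometer, jump and Yo-Yo tests, the statistician), and claim blinding only for roles and readings that are masked.

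The cost is renaming files and delaying the reading. No additional reader, scan or visit is needed. The drawback is that baseline image values are not available while the trial runs. Batch reading also means that baseline images are read after allocation, so the codes must hide the arm for these too.

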## Data collection and management

### Plans for assessment and collection of outcomes {18a}

#### Ultrasonography

Participants will report to the Human Performance Laboratory for ultrasound measurements after 72 h without any vigorous physical activity. They will be instructed to lay supine for 15 min to allow fluid shifts to occur before image collection. A 10-MHz linear probe scanning head (LA523 13-4) will be used to optimize spatial resolution and coat with water-soluble transmission gel and positioned on the skin surface to provide acoustic contact without depressing the dermal layer to collect the image. The length of the muscle fascicles and the PA, which is the angle of insertion of the fascicles into the muscle’s aponeurosis, represent the main structural parameters that can be detected via the conventional B-mode ultrasound modality [41]. Measures of CSA and FL will be obtained using a sweep of the muscle in the extended field of view mode with the gain set to 50 dB and image depth to 5 cm. The FL of rectus femoris (RF) and VM will be measured using “the intercept method” with this formula: FL = visible FL + predicted length [13].

All measures will be in the RF, vastus lateralis (VL), VM, and PT of the dominant leg. Subsequent measures will be taken using the same limb positioning and anatomical site and will be performed by the same examiner. After scanning, all images will be analyzed with image analysis software (ImageJ, version 1.45s), which quantifies muscle quality in the form of echo intensity (EI). A known distance of 1 cm as shown in the image will be used to calibrate the software program [13]. For the measures of RF and VM, the participant will be placed supine on an examination table, according to the American Institute of Ultrasound in Medicine, with the legs extended but relaxed and with a rolled towel beneath the popliteal fossa allowing for a 10 bend in the knee as measured by a goniometer. For measures of the VL and VM, participants will be placed on their non-dominant leg side with the legs together and relax to allow a 10 bend in the knee as measured by a goniometer. The measurement of RF CSA will be taken in the sagittal plane parallel to the long axis of the femur, and scanning occurs in the axial plane perpendicular to the tissue interface at 50% of the thigh length. Fifty percent of thigh length is determined as halfway from the anteroinferior iliac spine to the proximal border of the patella. VL and VM CSA measure at 50% of the distance from the most prominent point of the greater trochanter to the insertion. For all muscles, consecutive CSA images will be analyzed using the polygon tracking tool in the ImageJ software to obtain as much lean muscle as possible without any surrounding bone or fascia.

#### FL

FL will be measured using the extended field-of-view mode. A longitudinal sweep begins near the distal insertion along the muscle and continues towards the proximal head of the muscle. Fascicle length is determined by identifying a clear fascicle that extends continuously from the superficial aponeurosis to the deep aponeurosis.

#### MT

Measures of MT will be the same as described for CSA but with the probe oriented longitudinally to the muscle tissue interface for the three muscles. Within each muscle, MT measures perpendicularly from the superficial aponeurosis to the deep aponeurosis.

#### PA

The PA of the rectus femoris, vastuss lateralis, and vastus medialis will be measured using B-mode ultrasound at the same site as MT and CSA [1]. The transducer will be longitudinal to the muscle tissue interface, and 1 image will be analyzed offline. Muscle fiber will be determined as the intersection of the fascicles with the deep aponeurosis.

PT length will be measured via ultrasound scans (Esaote, Technos MPX, ultrasound) at knee joint angle of 90° (0° corresponding to full extension), as the distance between tendon insertions on the patella apex and the tibial tuberosity. Tendon CSA will be measured from transversal ultrasound scans (linear array transducer 5 cm, LA523, 10 MHz transducer). The reliability of this technique has been shown previously [45]. PT CSA is obtained as the average of two measurements performed at the proximal (CSAp) and distal (CSAd) insertions and at tendon mid-length (CSAm). The mean CSA of these three scans’ positions will be used for further analysis. PT length will be measured as the distance between the proximal insertion of the PT and the tibial insertion. The use of ultrasound to perform quantitative measurements of musculoskeletal tissues has shown reliability (tendon CSA: ICC of 0.91–0.98 and 0.96–0.98 for tendon length) [20].

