### Sample size {14}

The sample size was calculated by using “Gpower” software 3.1.9.2. For the determination of the effect size, we made a pilot study which included 10 participants from every single group. We measured the PA of VM for both groups. The mean (M) for football group was 10.59 and 8.17 for AG. Also, the standard deviation (SD) for FG was 2.80 and 2.01 for aerobic one. Based on this, the effect size was 0.992. The α level was 0.05, and the power was 0.95. The minimum numbers of sample were 46 participants.

We raise the sample to 60 for better result. Sixty untrained but healthy adult men are equally divided into two groups (mean ± SD age 55 ± 5). This sample includes a dropout of 15% and provides a moderately detectable change between a group with an alpha level of *p* < 0.05. Some of them had experienced some of the age-related neuromuscular problems or diseases, at least within the last year.

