#### Vertical jump test

The subject should, therefore, be instructed to jump as high as possible and land on the same spot. If the subject deviates too far from this point (a landing area/spot can be marked out), then the result should be disregarded and the jump repeated. Once the test configuration has been set up and the subject and assessor are ready, then the test will begin: the participants should walk into the take-off/landing area and, when instructed to by the assessor, jump as high as they can and land on the same spot. At the peak of their jump height, they should hit the vanes of the Vertec device to displace as many of them as possible. This should be repeated so that the athlete completes 3 jumps in total. This way, an average or best of the three jumps can be calculated. Jump height is determined by the difference between the participants’ standing reach height and the highest vane displaced. The results of the test are reported in terms of jump height (cm). To ensure a valid and reliable result, it is a good practice to take an average of the three jumps performed by the athlete. The following formula can be used to calculate the average jump height: Average jump height = (jump 1 + jump 2 + jump 3)/3. Alternatively, the best score (i.e., highest jump) out of the three jumps can also be used.

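### Pennation angle, a primary outcome and the sizing variable, is taken from one image per muscle per visit, which forgoes cheap precision but does not make the stated sample size wrong

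*Protocol article*

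**What the plan says.** Section PA, under Plans for assessment and collection of outcomes {18a}, covers the rectus femoris, vastus lateralis and VM and fixes the number of images: "The transducer will be longitudinal to the muscle tissue interface, and 1 image will be analyzed offline". It does not say how many angles or fascicles are read on that image.

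Outcomes {12} places PA under the primary outcome. Sample size {14} rests on it alone: "We measured the PA of VM for both groups". The inputs are that "we made a pilot study which included 10 participants from every single group", that "The mean (M) for football group was 10.59 and 8.17 for AG", and that "the standard deviation (SD) for FG was 2.80 and 2.01 for aerobic one". The section then states: "Based on this, the effect size was 0.992". It does not say how many images the pilot used.

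On reliability, Outcomes {12} cites a source for PA but gives no coefficient. The ICC range printed there, 0.92 to 0.999, is for muscle size. The ICCs in section PA (0.91–0.98 and 0.96–0.98) are for tendon CSA and tendon length. The planned test–retest check is described among the dynamometer measurements.

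**The concern.** PA is a small angle (pilot means of about 8 and 11 degrees). A reading from one image carries whatever error that probe placement and the choice of fascicle bring. This error adds to the between-man variance at each visit, so it widens the SD used in the comparison of arms. It enters a man's pre-to-post change twice. With one image, a poor scan cannot be diluted, and the trial produces no estimate of its own PA error. What is at stake is some precision on the outcome that the trial is built around, and the ability to show readers that the reading is repeatable.

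**Working it through.** **Inputs from Sample size {14}.** Means 10.59 and 8.17, a difference of 2.42; SDs 2.80 and 2.01; effect size 0.992; α 0.05; power 0.95; minimum 46; 60 enrolled with 15% dropout.

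**The plan's own figure.** Pooled SD = √((2.80² + 2.01²)/2) = 2.437. Effect size = 2.42/2.437 = 0.993, against 0.992 stated. A two-sample t test (noncentral t, 1:1) gives 23 per arm, or 46 in total, with a one-sided α of 0.05. Two-sided it gives 56. The article does not state the sidedness; that is a separate matter, so both are carried below.

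**Available men.** 60 × 0.85 = 51, about 25 per arm. Two-sided power at 25 per arm with effect size 0.992 is 93.0%.

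**Effect of averaging three images.** Let R be the single-image ICC, the share of total variance that is real difference between men. With independent image errors, SD(mean of 3)/SD(1 image) = √(R + (1 − R)/3), and the effect size is divided by this ratio. The article gives no R for PA, so a range is assumed, and the pilot is assumed to have used one image.

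| Assumed R | SD ratio | SD, mean of 3 | Effect size | Total N, one-sided | Total N, two-sided | Two-sided power, 25 per arm |
|---|---|---|---|---|---|---|
| one image | 1 | 2.437 | 0.992 | 46 | 56 | 93.0% |
| 0.98 | 0.993 | 2.421 | 0.999 | 46 | 56 | 93.3% |
| 0.92 | 0.973 | 2.371 | 1.020 | 44 | 54 | 94.2% |
| 0.90 | 0.966 | 2.355 | 1.027 | 44 | 52 | 94.5% |
| 0.80 | 0.931 | 2.269 | 1.066 | 40 | 48 | 95.8% |
| 0.70 | 0.894 | 2.180 | 1.109 | 38 | 46 | 97.0% |

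Example for R = 0.92: √(0.92 + 0.08/3) = √0.9467 = 0.973, and 2.437 × 0.973 = 2.371. Put the other way, one image inflates the SD over a mean of three by 2.8% at R = 0.92, 7.4% at 0.80 and 11.8% at 0.70.

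**Pre-to-post change.** Statistical methods {20a} also plans paired t tests within each arm. There, stable differences between men partly cancel and image error counts at both visits, so the gain can be larger. At R = 0.92 the error variance is 0.08 × 2.437² = 0.475. With an assumed true pre–post correlation ρ, the variance of change is 2 × 0.92 × 2.437² × (1 − ρ) + 2 × 0.475/k for k images. For ρ = 0.5 the SD of change falls from 2.53 to 2.40 with three images; for ρ = 0.8 it falls from 1.77 to 1.58. Neither R nor ρ is in the article, and these tests are not the comparison that the trial is sized on.

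**Is the stated N affected?** If the pilot used one image, its SDs of 2.80 and 2.01 already contain the single-image error and N already pays for it. Only if the pilot averaged three images and the trial reads one would N rise: at R = 0.92 from 46 to 48 (one-sided) or 56 to 58 (two-sided), and at R = 0.80 to 54 or 64. The article does not say which applies.

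**The case against.** The strongest reply is that this is a preference and not a fault. The article cites support for the reliability of PA by ultrasound. It also controls error by other means: the same examiner, limb position and site, 15 minutes supine, and 72 hours without vigorous activity. At the lowest ICC it prints for muscle ultrasound, 0.92, the gain is about 1 point of power. This stands as to size, though that ICC is for muscle size and not PA, and a fixed site and examiner do not remove image-to-image error.

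A reader might infer that PA is treated worse than the other outcomes, which get three repeats. The documents do not support that. For tendon CSA, "The mean CSA of these three scans’ positions will be used for further analysis", and these are three different sites, not repeats of one. The dynamometer takes the peak of three trials, which is not averaging. For the jump, "it is a good practice to take an average of the three jumps performed by the athlete", but the best of three is also allowed. The nearest comparators, fascicle length, muscle thickness and muscle CSA, have no stated number of repeats.

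There is also a point on timing. The article schedules baseline ultrasound for 1–10 March 2020 and the end of training for 15 July 2020, and it was published in December 2020. If those dates held, the baseline scans are done, and adding images at follow-up only would make the two visits differ in method. That limits the fix but not the point.

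**Conclusion.** The point holds as a minor, inexpensive improvement. One image per muscle per visit gives a noisier PA than a mean of three for any reliability below 1, and the article offers no PA figure to show that the loss is negligible. For the comparison of arms the loss is about 3% of the SD and 1 point of power at an assumed ICC of 0.92. It reaches 7–12% of the SD only at assumed ICCs of 0.8 to 0.7, which the article neither states nor excludes. All of this assumes independent errors between images; correlated errors shrink the gain.

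A reader might go further and conclude that the trial is undersized because of the single image. That does not follow. The pilot SDs may already include the error, so what is shown is forgone precision and not a wrong N.

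**What to change.** In section PA, replace the single-image rule with three images per muscle per visit, the probe lifted and repositioned between images, using the same method at both visits. The outcome assessor, whom section {17b} already describes as blinded, reads PA on each image, and the mean of the three is the outcome. Report the within-visit SD of the three readings as the trial's own PA measurement error. State in Sample size {14} how many images the pilot used.

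The cost is a little more scanning time at the two assessment visits and 60 men × 2 visits × 3 muscles × 2 extra images = 720 more offline readings. It needs no new visit, staff or device. If baseline scanning is already complete with one image, keep one image at both visits, report the choice as a limitation, and re-read stored images to estimate reader error. That would not capture error from probe placement.
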